#### Objective monitoring of motor function

To achieve objective and quantitative measures of patients’ motor function, we will perform a long-term monitoring of gait through continuous gait monitoring, we will use a single wearable sensor (STAT-ON^®^) SENSE4CARE SL., Cornellà de Llobregat (Spain) on a waist. STAT-ON is a Class IIa inertial medical device that is both lightweight and compact (86 g; 9 × 6.3 × 2.1 cm).^
32
^ It has successfully passed electromedical equipment tests, including those for home use. The device features two ultra-low triaxial nano-accelerometers, two microcontrollers, and a Bluetooth low-energy system, offering a battery life of 7 days under normal conditions. STAT-ON^®^ provides standard spatiotemporal gait parameters and uses advanced machine-learning algorithms to automatically detect motor patterns indicative of freezing of gait (FOG) and falls.^
33
^

In this study, following the sensor configuration based on individual clinical data (e.g., age, leg length), all patients will wear the STAT-ON sensor on the left waist via an elastic belt for five consecutive days (for 8 h per day during waking hours) per month. Recording sessions will be acquired monthly for a period of 12 months to collect the following spatiotemporal gait parameters and incident events: (1) number of steps; (2) step length; (3) step velocity; (4) step cadence; (5) number of FOG episodes; and (6) number of falls.^
34
^ Every 3 months, an encrypted and anonymized version of all collected data will be automatically sent to the PKNS of each center. The collected data will be summarized in a special report, including a graphical representation of the mean trend of parameters and spatiotemporal events of gait over time, as well as quantitative measures. In the intervention arm, physical activity levels and real-life motor autonomy will be objectively assessed to support proactive monitoring by the PKNS, who will add this objective information to the patient’s subjective report to adjust counseling and education during proactive calls made every 3 months. In the control group, data will be collected as a secondary outcome measure for final statistical analysis. At the end of the study, the data obtained from the wearable devices will be used to perform between-group analysis (comparison of cases vs controls) and within-group analysis (changes between V1 and V5 in each study group).

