#### Statistical analysis

No intermediate analysis is planned. The primary analysis will be by intention to treat principle as far as is practically possible. Analysis by protocol (PP) will be done after excluding patients with major deviations from the protocol. Descriptive statistics by treatment arm will be provided for all variables assessed in the study protocol with mean and standard deviation and median with range for continuous variables and absolute numbers and percentages for categorical variables.

The primary analysis will be based on the two-tailed *t*-test. Changes from baseline in the primary and secondary continuous variables (including longitudinal data obtained from the wearable device) will be analyzed by analysis of variance for repeated measures adjusted for baseline, or a corresponding nonparametric analysis as appropriate. Safety analysis will be performed by calculating the proportion of patients with AEs. The *p* values < 0.05 will be considered statistically significant, and all tests will be two-sided. The STATA Statistical Software, Release 16 (StataCorp. 2019. Stata Statistical Software: Release 16. College Station, TX: StataCorp LLC) will be used for statistical analysis.

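### Sensor counts of steps, freezing episodes and falls are analysed as continuous variables with no allowance for hours worn, so unequal wear between arms would appear as a treatment difference

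*Protocol article*

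**What the plan says.** The Statistical analysis section gives one method for change from baseline in continuous primary and secondary outcomes, "including longitudinal data obtained from the wearable device". These "will be analyzed by analysis of variance for repeated measures adjusted for baseline, or a corresponding nonparametric analysis as appropriate".

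The section on objective monitoring of motor function defines the wearable data. Of the six parameters, three are counts: number of steps, and then "5) number of FOG episodes; and (6) number of falls". The other three (step length, velocity, cadence) are not totals. On timing, "Recording sessions will be acquired monthly for a period of 12 months", and the sensor is to be worn "for five consecutive days (for 8 h per day during waking hours) per month", that is 5 × 8 = 40 h per session in both arms. The planned comparisons are "between-group analysis (comparison of cases vs controls) and within-group analysis (changes between V1 and V5 in each study group").

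The article names no rate, exposure term or count model for these variables.

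**The concern.** A count from a wearable is a rate multiplied by the time worn. The 40 h per session is a target. If one arm wears the sensor less, it records fewer falls and freezing episodes at the same true rate, and a comparison of raw counts reads this as a difference in falls.

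The design gives a reason for wear to differ. Randomization and blinding says that patients know their arm. In the intervention arm the recordings inform the nurse's three-monthly calls; in the control arm they are only collected. A control patient has less reason to keep wearing the belt, and the gap could open after baseline, once the calls begin. If controls wear it less, the bias hides a benefit; if the intervention arm does, it creates one.

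A second, smaller matter is that repeated-measures analysis of variance in its balanced form needs every session from every patient. With about 12 sessions in frail patients who rely on a smartphone app, some sessions are likely to be missed.

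Falls and freezing are central to the telemonitoring objective (Secondary outcomes, item 3), so an artefact here would bear directly on a claim the trial wants to make.

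**Working it through.** **The plan's own figure.** No figure is given for the sensor analysis. The stated 164 patients (82 per arm) belong to the PDQ-39. Root mean square SD = √((8.6² + 5.8²)/2) = 7.335; n per arm = 2 × (1.960 + 1.282)² × 7.335²/3.9² ≈ 74.3; 74.3/0.9 ≈ 82.6. This is close to the stated 82, and nothing below changes it. The checks use 74 per arm (82 × 0.9 = 73.8).

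**Size of the artefact.** Expected count = rate × hours. At the same rate, 32 h against 40 h gives a count ratio of 32/40 = 0.80, an apparent 20% reduction.

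**False-positive rate, no true effect, no baseline adjustment.** Inputs from the article: 12 sessions and 40 h planned. Assumptions, since the article gives none: 0.3 or 3 events per 40 h session; gamma between-patient variation with shape 0.5 or 1; session-to-session wear CV 20%; the wear gap present in all sessions. There were 1,000 runs per scenario. In balanced data the between-arm test of the repeated-measures analysis equals a t-test on patient means. Ranges run over the four settings of mean and shape.

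| Control vs intervention wear | ANOVA | Rank test | Negative binomial, log(hours) offset |
|---|---|---|---|
| 40 h vs 40 h | 4.4–5.8% | 4.2–5.1% | 4.6–6.3% |
| 32 h vs 40 h | 15–26% | 11–21% | 4.8–5.3% |
| 24 h vs 40 h | 50–85% | 35–74% | 4.6–6.3% |

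A separate run with control wear falling to 32 h only after baseline gave 14–25% for means and 11–20% for ranks.

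**With baseline adjustment** (first session as baseline, mean of the 11 later sessions as outcome, 2,000 runs per scenario):

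- Equal wear: 4.5–5.2%.
- Equal at baseline, then 36 h vs 40 h: 8–21%.
- Equal at baseline, then 32 h vs 40 h: 17–69% (18–70% in a separate run).
- 32 h vs 40 h already at baseline: 7–17%.

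Adjustment helps when the gap is already present at baseline. When the gap opens later, adjustment makes matters worse: it removes between-patient noise but leaves the bias.

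**Power at a true rate ratio of 0.6, no baseline adjustment.** With equal wear: ANOVA 51–86%, rank test 37–74%, negative binomial 54–88%. With control wear at 32 h: ANOVA 20–40%, rank test 14–31%, negative binomial with offset 51–88%.

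**Missed sessions, if the analysis is restricted to complete cases.** Share with all 12 sessions = (1 − q)¹² for an assumed independent miss probability q.

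- q = 5%: 0.95¹² = 0.540, or 44 of 82 per arm.
- q = 10%: 0.90¹² = 0.282, or 23 of 82 per arm.
- With misses clustered within patients (intra-patient correlation 0.1 to 0.5, beta-binomial), the shares rise to 67–86% and 44–73%.

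Implementation decides whether this loss occurs. In a small test data set with one missing cell, a balanced-only routine refused to run, while a long-format least-squares fit kept 79 of 80 rows.

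**The case against.** Planned wear is identical in both arms, and patients and carers are trained at screening and again at baseline. With equal wear the stated method holds its nominal error, and a count model adds only a few points of power. The documents give no evidence that wear will differ. All of this stands: the case rests on bias under unequal wear, not on power, and the wear gaps are assumptions.

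The nonparametric alternative also deserves credit. It partly answers the skewness of fall and freezing counts. It does not address exposure, because ranks of raw counts carry the same bias.

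Two stronger readings are tempting, and the document supports neither:

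- A reader might infer that patients who miss a session will be dropped. No complete-case rule is written, the outcome depends on how the model is fitted, and handling of missing sessions may sit in an analysis plan that is not shown. The most that can be said is that patients may be lost.
- A reader might extend the point to unplanned admissions, since a 12-month count has no baseline to change from. The sentence on repeated-measures analysis covers continuous variables and names only the wearable data. Admissions are described as a between-group comparison and are not assigned to this method.

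A minimum wear time for a valid session is likewise detail that an article may leave to the analysis plan. The choice of method for the sensor data is different, because the article states it.

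**Conclusion.** The point holds in a limited form. The plan places sensor counts among continuous variables and names a method with no exposure term. If actual wear differs by arm, the comparison of steps, freezing episodes and falls is biased, and neither the rank alternative nor baseline adjustment corrects it. At an assumed 32 h against 40 h the false-positive rate is roughly 11–25% by unadjusted means or ranks, and up to about 70% with baseline adjustment when the gap opens after baseline. With equal wear it is about 5%. These figures depend on assumed wear, event rates and dispersion.

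Loss of patients through missed sessions is possible, not established; the shares of 54% and 28% with all 12 sessions require both a complete-case analysis and independent misses.

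Only secondary outcomes are affected. The primary t-test on the PDQ-39 and the sample size are untouched. The change should be made because it is cheap and the alternative is clearly better.

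**What to change.** Replace the single method for wearable data with three statements, fixed before the data are compared by arm:

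- **Falls and freezing episodes:** a negative binomial model for repeated counts (patient random effect, or generalised estimating equations), with log(hours worn) in each session as offset.
- **Steps:** analysed per hour worn.
- **Step length, velocity and cadence:** a linear mixed model on all available sessions, with arm, month, arm × month and baseline value.

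The cost is wording in the analysis plan and somewhat more modelling, with a simpler fallback named in case a model does not converge. Hours worn must be available for each session; the article does not say whether they will be extracted, so this should be confirmed. No change to the sample size, visits or intervention is needed.

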### Intervention and monitoring

#### Intervention arm

Patients in the intervention arm will receive care from a PKNS for any medical (non-administrative) needs tailored to their necessities and standard medical treatment. A PKNS from each site will follow the patients enrolled.

- *PROACTIVE monitoring*: At baseline (V1), the PKNS contacts the patient to create a personal record using a semi-structured interview, including all symptoms of motor and non-motor characteristics and the type of risks that may occur. The PKNS instructs on risk prevention strategies related to the most relevant issues reported. After the initial proactive call to V1, PKNS will provide intermediate contacts every 3 months. At intermediate calls (V2, V3, V4), the PKNS focuses the interview on the problems/risks detected at baseline and provides tailored counseling and education. At the final visit (V5), the investigator will complete the follow-up of all the incident events and medical issues occurred during the study.- *REACTIVE monitoring*: During the study period, the patient and care provider may contact the PKNS at any time prior to the previously scheduled in-person visit for urgent needs by telephone (3h/day, 5 days/week, Mon-Fri) or by e-mail (within 48 h).

The PKNS can (1) also address the specific problem by interacting with the participant’s primary care physician and other healthcare providers or (2) refer to the treating neurologist (who is not the blind rater) for teleconsultation or in-person visit, according to a semi-structured algorithm that assigns four levels of priority similar to emergency room “triage”.^
19
^ Briefly, whenever a referral to a neurologist is needed, PKNS assigns a 4-level code triage, where increased urgency would lead to reduced assessment time and the opportunity for a teleconsultation with an experienced neurologist. We proposed this approach to triage patients query during COVID-19 pandemic, including a detailed flowchart.^
19

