#### Control arm

Patients in the control arm will undergo a 30-min in-person visit with the neurologist at baseline (V1), 6 months (V3), and 12 months (V5) after randomization.

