#### Secondary outcomes

1. To evaluate the feasibility and effectiveness of an innovative telenursing approach consisting of proactive and reactive remote monitoring aimed at optimizing continuity of care by improving motor and non-motor disability control, including through better adherence (compliance) to the prescribing regimen. Outcome measures will be the changes in MDS-UPDRS (Parts I, II, and III) and NMSS scores in all participants. Disease-specific scales will also be used: (a) UMSARS in subjects diagnosed with MSA and (b) PSPRS in those diagnosed with PSP. In addition, changes in scores on the functional disability (CFS) and autonomy in activities of daily living (IADL, ADL) scales will be used. Compliance to prescribing regimen will be measured by the changes in scores on the Italian version of the MMAS-8 on adherence to pharmacological therapy.^
31
^2. To investigate the cost-effectiveness of the management model by telenursing compared to standard care in terms of (a) reducing the number of unplanned hospital admissions and (b) reducing complications/comorbidities to minimize direct and indirect costs to the national healthcare system. We will analyze differences between the two study groups in the number of unplanned hospital admissions in 12 months through an interview to patient and/or care provider (calculating outpatient visits, emergency room admissions, hospitalizations directly or indirectly associated with neurological pathology). In addition, differences between the two study groups in comorbidity frequency (total events, disease-related events) through (a) patient and/or caregiver interview and (b) the Italian version of the Cumulative Illness Rating Scale for Geriatrics^
30
^ will be evaluated. To estimate the incremental cost per quality-adjusted life-year gain (QALY)^
29

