### Safety

All adverse events (AEs) including all Serious adverse events will be collected, properly investigated, and documented in the original documents and appropriate sections of the eCRF during the entire study period, from the signing of informed consent to the last protocol-specific procedure, including the follow-up period for safety.

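### Non-serious adverse events are looked for more often in the intervention arm by design, and the by-arm AE proportion has no common-source rule

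*Protocol article*

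**What the plan says.** All references are to the Protocol article.

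- **Intervention arm.** "After the initial proactive call to V1, PKNS will provide intermediate contacts every 3 months". These calls are V2, V3 and V4. Between them, "the patient and care provider may contact the PKNS at any time prior to the previously scheduled in-person visit for urgent needs by telephone", with e-mail as an alternative. At V5, "the investigator will complete the follow-up of all the incident events and medical issues occurred during the study".
- **Control arm.** Patients have a "30-min in-person visit with the neurologist at baseline (V1), 6 months (V3), and 12 months (V5) after randomization". No nurse contact or reporting line is described.
- **Clinical assessment.** The blind rater sees both arms at V1, V3 and V5. At V3 the rater records incident medical events, falls and hospitalisations. The list of items for V1 and V5 contains no such entry.
- **Safety.** All AEs are to be "documented in the original documents and appropriate sections of the eCRF during the entire study period", from consent to the last procedure. No source is named.
- **Statistical analysis.** "Safety analysis will be performed by calculating the proportion of patients with AEs". A general sentence in the same section provides descriptive statistics by treatment arm for every variable.
- **Secondary outcomes, item 2.** The plan evaluates "differences between the two study groups in comorbidity frequency (total events, disease-related events") from a patient or caregiver interview and from the Cumulative Illness Rating Scale for Geriatrics. Unplanned admissions over 12 months also come from an interview.

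**The concern.** Both arms are observed for 12 months, but the intervention arm is asked about events more often and can report them at any time. Minor events in controls may have to be recalled over six months. The nurse calls focus on the problems and risks found at baseline, which may be the same kinds of problem that are later recorded as AEs. If every event that comes to notice is entered and the proportion with an AE is then set out by arm, part of any difference reflects how often patients were asked. The bias runs against the intervention: telenursing could appear to cause more AEs when it only finds more. If nurse-detected events also entered the comorbidity count, a true reduction in complications, which is part of secondary objective 2, would be diluted.

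**Working it through.** **1. Occasions for reporting after baseline**

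| | Intervention | Control |
|---|---|---|
| Nurse contacts | months 3, 6, 9 | none |
| Visits | months 6, 12 | months 6, 12 |
| Distinct scheduled time points | 4 | 2 |
| Longest gap | 3 months | 6 months |
| Open telephone/e-mail line | yes | none described |

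**2. Which counts are exposed**

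- *Non-serious AEs:* exposed. Safety takes AEs from any source, and Statistical analysis does not restrict the source.
- *Comorbidity events:* exposed only if the interview includes nurse contacts. The text does not say whether it does. The shared channel is also written unevenly: event recording by the blind rater is listed at V3 but not at V5, and the V5 event follow-up appears only under Intervention arm.
- *Unplanned admissions:* better protected. They come from a 12-month interview in both groups and are hard to forget.
- *Sensor-detected falls and freezing episodes:* not exposed. All patients wear the device on the same monthly schedule (Objective monitoring of motor function).
- *PDQ-39:* not exposed.

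**3. Illustration of size**

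The document gives no AE rate and no detection rate, so there is no planned figure to reproduce, and every rate below is an assumption. Let the true rate be λ per patient-year, equal in both arms, and let the detection probabilities be d_I (intervention) and d_C (control).

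- Ratio of recorded events = d_I / d_C
- Proportion with at least one recorded event = 1 − exp(−λ × d), with Poisson events over one year

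With d_I = 0.90:

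| d_C | Event ratio | λ = 0.5 | λ = 1 | λ = 5 |
|---|---|---|---|---|
| 0.80 | 0.90/0.80 = 1.13 | 36% v 33% | 59% v 55% | 98.9% v 98.2% |
| 0.70 | 0.90/0.70 = 1.29 | 36% v 30% | 59% v 50% | 98.9% v 97.0% |
| 0.60 | 0.90/0.60 = 1.50 | 36% v 26% | 59% v 45% | 98.9% v 95.0% |

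For example, at λ = 1 and d_C = 0.70: 1 − exp(−0.90) = 0.593 and 1 − exp(−0.70) = 0.503. At λ = 5: 1 − exp(−4.5) = 0.989 and 1 − exp(−3.5) = 0.970.

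The event ratio does not depend on λ. The any-AE proportion depends on it strongly: when nearly everyone has an AE, the gap almost vanishes.

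**4. If the λ = 1, 90% v 70% case were tested**

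The plan states no test for AEs. With 82 per arm, the pooled proportion is (0.593 + 0.503)/2 = 0.548. The standard error is √(2 × 0.548 × 0.452/82) = 0.078, so the shift is 0.090/0.078 = 1.16 standard errors. The chance of a two-sided p < 0.05 is about P(Z > 1.96 − 1.16) = 21%, with no true difference.

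**5. If nurse contacts fed the comorbidity count**

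A true 25% reduction would be recorded as 0.75 × 1.29 = 0.96 at 90% v 70%, or 0.75 × 1.50 = 1.13 at 90% v 60%.

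**The case against.** The strongest reply is that much of the ascertainment is already common. The blind rater sees both arms at the same visits and records events at V3. The comorbidity comparison names its sources, an interview and a rating scale, and nurse logs are not among them. The AE sentence states no between-arm test. How AEs are elicited, and whether the eCRF has a source field, are details that an article may leave to the full protocol. Controls may also contact their neurologist between visits under usual care.

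Most of this stands, and it limits the point in three ways that a reader might otherwise miss.

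- A reader might count sensor reports as another intervention-only source. They are not: wear is identical in both arms, and only the nurse's use of the reports differs.
- A reader might infer that the complications comparison will be diluted or reversed. That follows only if its interview takes in nurse contacts, which the text does not say.
- A reader might infer that telenursing will look harmful. The direction of the bias is clear, but its size is unknown, and at high AE rates the any-AE proportion barely moves.

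The reply does not remove the AE point. Collection of all AEs over the whole study, on its face, includes what the nurse learns. The by-arm summary has no common-source rule, and the contact schedules differ by design. This is something the article fixes, not a detail it omits.

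Two objections to a remedy also carry weight. Dropping nurse-detected events from the comparative table could hide harm, so the all-source table must stay. And earlier nurse calls may change what patients recall or repeat at V3 and V5, so a common interview reduces the bias without guaranteeing its removal.

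**Conclusion.** The point holds for non-serious AEs. Intervention patients have four scheduled post-baseline time points and an open line, against two time points for controls, and recorded AEs could be higher in the intervention arm with equal true rates. For comorbidity events it holds conditionally, and the uneven description of event recording at V5 leaves the condition open. It does not extend to sensor-detected events or to the PDQ-39 analysis, and it has less force for serious events and hospitalisations.

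The size rests wholly on assumed rates. Across the detection gaps shown, the recorded event ratio runs from 1.13 to 1.50. At 90% against 70%, the any-AE proportion differs by about 9 points at one AE per patient-year and about 2 points at five. The document supports neither rate over the other.

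**What to change.** 1. In Clinical assessment, Secondary outcomes item 2 and Statistical analysis, state that the between-arm comparison of non-serious AEs and comorbidity events uses events elicited by the blind rater with the same interview at V3 and V5 in both arms. Add event recording to the blind rater's V5 list.
2. Tag the source of each event in the eCRF (V3/V5 interview, nurse call, telephone or e-mail, other), if it is not already recorded.
3. Show the all-source AE table by arm alongside, with events known only from nurse or telephone/e-mail contact identified, so that no known AE is hidden.
4. Compare serious AEs and hospitalisations from all sources, and leave the sensor comparison as planned.

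The cost is a few sentences, possibly one eCRF field, and two AE tables instead of one. The article describes recruitment as ongoing, so events already entered may need their source back-coded. Some bias will remain if nurse calls affect recall at V3 and V5, and the report should say so.
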